## Abstract

**Background:**

Natural orifice transluminal endoscopic surgery (NOTES) is the consequence of further development of minimally invasive surgery to reduce abdominal incisions and surgical trauma. The potential benefits are expected to be less postoperative pain, faster convalescence, and reduced risk for incisional hernias and wound infections compared to conventional methods. Recent clinical studies have demonstrated the feasibility and safety of transvaginal NOTES, and transvaginal access is currently the most frequent clinically applied route for NOTES procedures. However, despite increasing clinical application, no firm clinical evidence is available for objective assessment of the potential benefits and risks of transvaginal NOTES compared to the current surgical standard.

**Methods:**

The TRANSVERSAL trial is designed as a randomized controlled trial to compare transvaginal hybrid NOTES and laparoscopic-assisted sigmoid resection. Female patients referred to elective sigmoid resection due to complicated or reoccurring diverticulitis of the sigmoid colon are considered eligible. The primary endpoint will be pain intensity during mobilization 24 hours postoperatively as measured by the blinded patient and blinded assessor on a visual analogue scale (VAS). Secondary outcomes include daily pain intensity and analgesic use, patient mobility, intraoperative complications, morbidity, length of stay, quality of life, and sexual function. Follow-up visits are scheduled 3, 12, and 36 months after surgery. A total sample size of 58 patients was determined for the analysis of the primary endpoint. The confirmatory analysis will be performed based on the intention-to-treat (ITT) principle.

**Discussion:**

The TRANSVERSAL trial is the first study to compare transvaginal hybrid NOTES and conventionally assisted laparoscopic surgery for colonic resection in a randomized controlled setting. The results of the TRANSVERSAL trial will allow objective assessment of the potential benefits and risks of NOTES compared to the current surgical standard for sigmoid resection.

**Trial registration:**

The trial protocol was registered in the German Clinical Trials Register (
DRKS00005995) on March 27, 2014.

**Electronic supplementary material:**

The online version of this article (doi:10.1186/1745-6215-15-454) contains supplementary material, which is available to authorized users.

## Background

### Rationale

Since natural orifice transluminal endoscopic surgery (NOTES) was described by Kalloo *et al.* it has gained the attention of surgeons and gastroenterologists worldwide
[1]. Aiming to further minimize surgical trauma by reducing transabdominal incisions, NOTES may be seen as an attempt to further develop minimally invasive surgery. The potential benefits of avoiding abdominal incisions with NOTES are less postoperative pain, faster convalescence, and reduced risk of incisional hernias and wound infections. However, these potential advantages have not yet been proven conclusively.

Several NOTES concepts are currently in development. Though pure NOTES is performed exclusively via transluminal access, hybrid NOTES combines transluminal access with conventional laparoscopic access. Pure NOTES procedures are technically challenging and have been applied only in sporadic clinical cases
[2–4]. In contrast, hybrid NOTES procedures allow the use of rigid instruments and are technically very similar to conventional laparoscopic procedures. Surgical access can be created and closed under laparoscopic view using a transabdominally placed trocar and the specimen removed via transluminal access. Due to these benefits, hybrid NOTES procedures have advanced to clinical application
[5–9].

Based on gynecological experience, transvaginal access was the first transluminal access and advanced to the most frequently applied route for NOTES
[7]. Several studies have confirmed the feasibility and safety of transvaginal cholecystectomy
[5, 6, 8] and colonic resection
[10, 11] using the hybrid NOTES approach.

NOTES is still met with broad skepticism because its potential benefits are generally doubted and potential access-related complications feared. However, despite increasing clinical application, there is no firm evidence for objective assessment of the potential benefits and risks of NOTES. In particular, no study has compared transvaginal hybrid NOTES sigmoid resection and conventional laparoscopic surgery in a randomized controlled setting.

### Objective

The TRANSVERSAL (‘Transvaginal hybrid NOTES versus conventionally assisted laparoscopic sigmoid resection for diverticular disease’) trial is a randomized controlled trial intended to evaluate transvaginal hybrid NOTES and conventionally assisted laparoscopic sigmoid resection. The study design allows objective assessment of the potential benefits and risks of transvaginal NOTES compared to the current laparoscopic standard for sigmoid resection.

## Methods/Design

### Trial design

The TRANSVERSAL trial is a randomized controlled multicenter trial comparing transvaginal hybrid NOTES sigmoid resection (experimental intervention) to conventionally assisted laparoscopic sigmoid resection (control intervention) and is designed as a parallel group superiority trial. The trial scheme is illustrated in Figure 
1.

**Figure 1 Fig1:**
[figure not shown]
**Trial scheme.**

### Study population and eligibility criteria

All female patients aged ≥18 years and referred to elective sigmoid resection due to diverticulitis of the sigmoid colon will be screened for inclusion (Table 
1). Patient screening comprises an investigation of the patient’s medical history and findings, a physical examination, and a routine gynecological examination performed by a gynecologist in all cases.

**Table 1 Tab1:** **Inclusion and exclusion criteria**

Inclusion criteria	Exclusion criteria
• Female patients indicated for elective sigmoid resection due to at least two episodes of uncomplicated diverticulitis or first episode of complicated diverticulitis classified as IIa or IIb according to Hansen and Stock [12]	• ASA classification higher than III
• Age ≥18 years	• Inability to consent
• Informed consent	• Pregnancy
	• Genital infections
	• Neoplasms of vulva, vagina, or cervix
	• Douglas endometriosis
	• History of pelvic floor repair
	• Chronic inflammatory bowel disease
	• Fibromyalgia
	• Psychiatric disorder
	• Regular use of analgesics, steroids, or antidepressants

ASA, American Society of Anesthesiologists.

### Organizational structure and responsibilities

The principal investigator ([name]) is primarily responsible for the preparation of the study protocol and the case report form (CRF), the organization of steering committee meetings, and the dissemination policy. At each participating center, a lead investigator ([name], [name], [name]) is responsible for screening, recruitment, data collection, and completion of the CRFs. All lead investigators are members of the study steering committee, which oversees study progress and safety. Prior to creation of the study protocol, standardization of the intervention, perioperative management, patient recruitment, and study visits was homogenized during steering committee meetings. Further meetings are intended to occur before enrollment of the first patient. Surgery will be performed by the principal investigator and the lead investigators with an experience of >50 laparoscopic colorectal resections and >20 transvaginal hybrid NOTES procedures. Further meetings are intended to occur before enrollment of the first patient. Patient enrollment, randomization, and data management will be carried out by the Study Center of the German Surgical Society (SDGC) at the University of Heidelberg.

### Sample size

A total of 58 patients will be randomized for this trial, 29 patients per group.

### Recruitment and trial timeline

Female patients aged ≥18 years presenting for elective sigmoid resection due to at least two episodes of uncomplicated diverticulitis or the first episode of complicated diverticulitis classified as IIa or IIb according to Hansen and Stock
[12] will be further screened for eligibility criteria by surgical consultants at the participating centers. Surgical consultants from all centers will be informed about the TRANSVERSAL trial and its inclusion criteria during department meetings. For informed consent, the patients will be verbally introduced to the trial by a member of the research group and in writing via the Patient Information Sheet (Additional files
1,
2,
3 and
4). Informed consent will be obtained from each patient before inclusion in the study.

Before inclusion in the study, the feasibility of both techniques will be confirmed by diagnostic laparoscopy to avoid inclusion of patients who are immediately converted to open surgery. Potential reasons for conversion to open surgery are pronounced adhesions or tissue scarification due to prior surgery or prior episodes of diverticulitis. However, the decision is subject to the assessment of the respective surgeon. Therefore, the reasons for technical infeasibility and other reasons for exclusion will be recorded anonymously alongside descriptive data for all screened patients and presented in the final study report. If experimental or control interventions seem technically feasible to the surgeon during diagnostic laparoscopy, patients will be enrolled at the participating centers. A total of 100to 150 female patients are expected to be referred for elective surgery for diverticulitis. Based on the experiences in our previous study, we expect a recruitment rate of 60 to 70%
[11]. Recruitment strategies, such as provisions or financial compensation, are not intended. The recruitment of 58 patients is planned to be finished within 24 months. The time interval from first patient in to last patient out will be 60 months.

### Randomization, allocation concealment, and blinding

The SDGC will enroll and randomize patients immediately after diagnostic laparoscopy and confirmation of the technical feasibility of both procedures by the surgeon. The patients will be randomized using an online randomization tool (
http://www.randomizer.at). Randomization will be stratified by computer-generated permuted blocks of varying size with a 1:1 ratio to the experimental and control intervention groups. Patient allocation will be revealed to the surgeon after randomization by a study nurse using a written form, which will be destroyed immediately after unveiling. A standardized wound dressing will be applied after both techniques to cover the trocar and minilaparotomy sites (Figures 
2 and
3). Investigators and patients will be blinded to the group affiliation until removal of the wound dressing at discharge. The study visits will be performed by investigators who are not involved in the surgical procedures. The wound dressing will be changed with the patient blinded using blinding glasses on postoperative day (POD) 2 and at 3-day intervals thereafter. At each center, a study nurse will be in charge of changing the wound dressing and will not be involved further in the trial. If unscheduled wound dressing is necessary, the indication and time point will be documented. In the case of wound complications, patients and investigators will be unblinded. The surgical report and all patient files will be blinded for surgical technique. To evaluate the success of the blinding procedure, the patient's and investigator's suspicion of group affiliation will be documented before measuring the primary endpoint and before regular unblinding at discharge. In the case of adverse events, unblinding may be performed prematurely based on the assessment of the principal investigator. The patients' allocated interventions can be revealed at any time by accessing the allocation list within the trials office.

**Figure 2 Fig2:**
[figure not shown]
**Trocar positions and standardized wound dressing for the experimental intervention.** *transvaginal trocar.

**Figure 3 Fig3:**
[figure not shown]
**Trocar positions and standardized wound dressing for the control intervention.** †a 5 mm trocar incision will be extended to Pfannenstiel minilaparotomy.

### Interventions

#### Experimental intervention

Transvaginal hybrid NOTES sigmoid resection will be performed in the lithotomy position. A 5-mm trocar will be placed umbilically via an incision and a 12-mmHg carbon dioxide pneumoperitoneum established. Three additional 5-mm trocars will be placed under laparoscopic view: one suprapubically, one in the right lower quadrant, and one in the left lower quadrant (Figure 
2). Before every skin incision, a local anesthetic (3 mL of bupivacaine 0.25%) will be applied subcutaneously. After laparoscopic exploration of the abdomen, standard medial-to-lateral mobilization of the sigmoid colon will be performed. For introduction of the stapler device, a 12-mm transvaginal trocar will be inserted through the posterior fornix after antiseptic wash-out of the vagina. After distal dissection of the sigmoid colon, a dorsal colpotomy will be performed and the colon carefully externalized through a transvaginal wound protector. Proximal dissection of the sigmoid colon will be performed extracorporally using an energy device. A purse-string suture will be placed at the proximal end of the colon and the circular stapling anvil inserted into the colon. After intra-abdominal relocation of the descending colon, the colpotomy will be sutured transvaginally with resorbable thread. An end-to-end anastomosis will be performed under laparoscopic view using a circular stapling device. Air-leak testing will be performed routinely by transanal insufflation of air with the anastomosis immersed in saline solution. After suturing the fascia and cutis, the standardized wound dressing will be placed.

#### Control intervention

Conventionally assisted laparoscopic sigmoid resection will be performed in the lithotomy position. A 5-mm umbilical trocar will be inserted via an incision. After establishing a 12-mmHg carbon dioxide pneumoperitoneum, three additional transabdominal trocars will be placed under laparoscopic view: one 12-mm trocar in the right lower quadrant, one 5-mm trocar in the left lower quadrant, and one 5-mm trocar at the suprapubic midline (Figure 
3). Before every skin incision, local anesthetic (3 mL of bupivacaine 0.25%) will be applied subcutaneously. After medial-to-lateral mobilization of the descending colon, a laparoscopic stapling device will be used to dissect the distal end of the sigmoid colon. Pfannenstiel minilaparotomy will be performed to extract the sigmoid colon, extending the incision for the trocar placed within the suprapubic midline. After extracorporeal dissection of the proximal end, the anvil for the circular stapling device will be placed within the colon and secured with a purse-string suture. For colorectal anastomosis, the colon will be reintroduced into the peritoneal cavity. An end-to-end stapler anastomosis and air-leak test will be performed as described above. After suturing the fascia and cutis, the standardized wound dressing will be placed.

### Perioperative management, discharge, and follow-up

Perioperative thrombosis prophylaxis will be performed according to current German guidelines
[13]. Single-shot antibiotics (ampicillin/sulbactam) will be given 30 minutes before surgery. Intraoperative anesthesia will comprise intravenous administration of piritramide. Postoperatively, pain medication will be administered according to the World Health Organization (WHO) analgesic ladder based on the judgment of the treating ward physician beginning directly after surgery in the recovery room
[14]. Nonsteroidal anti-inflammatory drugs (metamizol) will be administered solely or in combination with a weak (tilidine) or strong opioid (piritramide, oxycodone). Peridural analgesia is not part of the pain management in this study. On the day of surgery and POD 1, analgesics will be administered intravenously. Beginning from POD 2, analgesics will be applied orally in cases of tolerated oral intake. Daily blood samples are scheduled for POD 1 to 5. Patients will be encouraged for discharge from POD 5 onward upon complete fulfillment of the discharge criteria (see ‘Discharge criteria’). Patients who receive the experimental intervention will be recommended to attend an ambulatory gynecological checkup 10 days after surgery. All patients will be followed up at an ambulatory checkup scheduled 3, 12, and 36 months after surgery. The ambulatory checkup will comprise taking a history, a clinical examination, and an assessment of secondary endpoints. Patients will be notified in writing and by phone in case they fail to return for their follow-up visits. If reaching the patients directly is not possible, their general practitioner will be contacted. Missing follow-up data will then be completed by phone.

### Discharge criteria

Patients will be discharged upon complete fulfillment of the following criteria:

 ≥POD 5 Full oral intake ≥1 passage of stool Regular primary wound healing Adequate pain control (VAS ≤3 under mobilization) with NSAID and low-potent opioid (tilidine) In-ear body temperature ≤38°C Decreasing laboratory markers of inflammation (CRP, leukocytes) CRP, C-reactive protein; NSAID, nonsteroidal anti-inflammatory drug; POD, postoperative day; VAS, visual analogue scale.

### Risk-benefit ratio

The potential benefits of transvaginal hybrid NOTES sigmoid resection are expected to be less postoperative pain, faster convalescence, and reduced risk of wound infections and incisional hernia compared to conventional methods. The potential complications related to NOTES access are disturbed vaginal wound healing, impaired sexual function, and transvaginal microbiological contamination of the peritoneal cavity. In a recent study, we found a positive bacterial culture in the Douglas pouch following colpotomy in 2 of 27 (7%) patients undergoing transvaginal cholecystectomy. However, in both cases peritoneal contamination did not impact morbidity
[15]. Two studies assessed postoperative sexual function after transvaginal NOTES cholecystectomy and did not find impairment after a follow-up of 12 months
[16, 17]. In a cohort study of 44 patients undergoing transvaginal hybrid NOTES sigmoid resection we found major complications (≥grade 3) in 2 patients (4.4%) and minor complications (<grade 3) in 10 patients (22.2%)
[11]. No mortality occurred
[11]. Overall, these rates are comparable to previously published literature on assisted laparoscopic sigmoid resection for diverticular disease
[18, 19]. Consequently, no evidence yet indicates higher morbidity after transvaginal hybrid NOTES sigmoid resection compared to the assisted laparoscopic approach.

### Outcome parameters

#### Primary endpoint

The primary endpoint is intensity of pain measured by a visual analogue scale (VAS) during mobilization of the patient 24 hours postoperatively. Patients and investigators will be blinded for this measurement. Before mobilization of the patient, the investigator will provide a standardized explanation of the VAS using a written text. The patient will be asked to record current pain intensity by drawing a vertical line on a horizontally positioned 100-mm VAS ranging from 0 (no pain) to 10 (worst imaginable pain). For mobilization, patients will be asked to take a seated position at the edge of the bed, to stand up, and finally to lie down in bed again. Immediately after mobilization, the patient will be asked to record the maximum pain intensity experienced during mobilization.

#### Secondary endpoints

Secondary endpoints will be measured intraoperatively, at daily study visits, and 3, 12, and 36 months postoperatively. Intraoperative parameters comprise operation time, length of minilaparotomy, height of the anastomosis and the length of the unfixed specimen. The number of harvested lymph nodes will be determined postoperatively by pathological examination. The schedule for study visits and follow-up is provided in Table 
2. Pain intensity will be measured at rest and during mobilization in the same way as the primary endpoint. The dose and identity of applied analgesics will be recorded daily. Daily analgesic use will be graded using a numeric scale from one to three according to the WHO analgesic ladder
[14]. Cumulative analgesic use will be assessed by adding daily WHO analgesic ladder scores. Daily patient mobility will be measured in meters by an electronic pedometer device, which will be placed on the wrist of the nondominant hand of the patient. Cumulative patient mobility will be assessed by adding daily distances. Inflammatory parameters (leukocytes, C-reactive protein) will be measured daily from POD 1 to POD 5. The discharge criteria (See ‘Discharge criteria’) will be evaluated beginning from POD 5. After discharge, the patients will be asked to record daily analgesic use and activity on a scale ranging from 0 (inactivity) to 5 (return to usual activities) until they return to usual activities and stop pain medication on a standardized form, which will be evaluated at the 3-month follow-up visit. Morbidity according to Dindo *et al*.
[20] will be assessed at discharge, 3, 12, and 36 months postoperatively. The following patient-reported outcomes will be assessed preoperatively and 3, 12, and 36 months postoperatively: quality of life measured by the Gastrointestinal Quality of Life Index (GIQLI)
[21], sexual function measured by the Female Sexual Function Index (FSFI)
[22], and cosmetic satisfaction measured by the Body Image Scale
[23].

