#### Statistical analysis

Statistical analysis will be performed using the R statistical software (
http://www.r-project.org). A two-sided *P* value <0.05 will be considered significant. For baseline characteristics, descriptive statistics will be used. For analysis of the primary outcome, a Mann-Whitney *U* test will be applied. For categorical secondary endpoints, chi-square statistics will be used. To compare continuous secondary endpoints (operating time, length of hospital stay, analgesic use, time to return to normal activity), Mann-Whitney *U* tests will be applied. No interim analysis is planned for this study. For the time course of pain at provocation and at rest, a mixed model with mean VAS scores will be applied.

Missing values will be replaced with the last available value (the last observation carried forward (LOCF) approach). Data from patients who withdraw from the study will be disregarded unless exclusion is based on postoperative patient wishes and the patient agrees to the use of the already obtained data.

The confirmatory analysis will be performed based on intention-to-treat (ITT) patients and with respect to ITT principles. A standard sensitivity analysis will be performed on the per-protocol population.

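### The analgesic-use endpoint reduces recorded drug and dose to a WHO step of 1 to 3, so opioid-dose differences within a step are lost and a drug-free day has no stated score

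*Protocol article*

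**What the plan says.** Under Secondary endpoints the protocol article first states what is collected: "The dose and identity of applied analgesics will be recorded daily". It then states how this becomes an endpoint: "Daily analgesic use will be graded using a numeric scale from one to three according to the WHO analgesic ladder", and "Cumulative analgesic use will be assessed by adding daily WHO analgesic ladder scores". Table 2 schedules daily analgesic use on POD 1 and on POD 2 to 5, and cumulative use on POD 5, at discharge and at 3 months. After discharge, patients keep a daily record "until they return to usual activities and stop pain medication on a standardized form".

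Under Perioperative management, discharge, and follow-up, analgesics follow the WHO ladder "based on the judgment of the treating ward physician". A non-opioid "will be administered solely or in combination with a weak (tilidine) or strong opioid (piritramide, oxycodone"). Under Statistical analysis, analgesic use is listed among the continuous secondary endpoints and compared by a Mann-Whitney U test.

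**The concern.** The primary endpoint is VAS pain during mobilization at 24 hours. Analgesia before that measurement is not fixed; the ward physician adjusts it. If one operation hurts less, part of the benefit may therefore appear as less analgesic rather than as a lower VAS. Similar VAS scores reached on different opioid doses would mean something other than similar scores on similar doses. Analgesic use on POD 1 is the measure a reader would consult to tell these apart.

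The endpoint as defined keeps only the step. Two patients on a strong opioid receive the same score however much each was given, although the dose has been recorded.

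The cumulative score has a second problem. The scale begins at one, yet recording continues until pain medication stops, so days without analgesics are to be expected. The article does not say what such a day contributes to the sum.

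**Working it through.** **The plan's own figures.** The article gives no figure for analgesic use. The number per arm used below comes from its sample size section and reproduces. A two-sample t test with standardized effect 1, two-sided alpha 0.05 and power 0.90 solves to 22.02, so 23 per arm (power 0.912). With 20% drop-out, 23 / (1 - 0.20) = 28.75, so 29 per arm and 58 in total.

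**1. Drug-free days.** Take a patient on step 3 on POD 1 and 2 and on nothing on POD 3 to 5.
- Drug-free days add nothing: 3 + 3 + 0 + 0 + 0 = 6.
- Drug-free days take the lowest stated code: 3 + 3 + 1 + 1 + 1 = 9.

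This can change ranks, which is what the Mann-Whitney test uses. A second patient on steps 3, 2, 1, 1, 1 sums to 8 under either reading. The first patient ranks below the second in one case (6 < 8) and above in the other (9 > 8).

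**2. Dose within a step.** If every patient in both arms is on a strong opioid, every score is 3. All values are tied and the test cannot reject, whatever the doses.

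**3. Power on dose and on score (assumed inputs, not document figures).** Simulated Mann-Whitney tests, 29 per arm, two-sided 0.05, 3,000 runs per setting. The log-dose SD is 0.6. The same share of patients in each arm is on a strong opioid; the rest are on step 2 and count as zero strong-opioid dose.

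| Share on strong opioid | Dose ratio | Power on dose | Power on ladder score |
|---|---|---|---|
| 100% | 1.5 | 0.69 | 0 |
| 100% | 2 | 0.99 | 0 |
| 80% | 1.5 | 0.33 | about 0.05 |
| 80% | 2 | 0.70 | about 0.05 |
| 50% | 1.5 | 0.10 | about 0.05 |
| 50% | 2 | 0.17 | about 0.05 |

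In the 80% and 50% rows the score rejects at about the type I error level, because the arms do not differ in step.

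**4. When the arms do differ in step.** With step 3 in 80% versus 40% of patients and the rest on step 1, the score has power of about 0.88. With 70% versus 40% it is about 0.64.

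**The case against.** The strongest reply is that the ladder score is a coarse but real measure. It separates non-opioid, weak-opioid and strong-opioid days, and step 4 of the working shows that it can detect a difference between steps. Dose is recorded, nothing in the article bars a dose analysis, and conversion tables commonly sit in an analysis plan that is not shown here. All of that stands, and it limits the point. But the article does more than stay silent on detail: it fixes the endpoint as the step and the cumulative endpoint as the sum of steps.

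A reader might infer several stronger things that the article does not support.

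- **That the score cannot show higher opioid use at all.** It can, when higher use means a higher step.
- **That the score saturates in the first 24 hours.** The article gives neither the share on strong opioids nor dose counts, and it allows a non-opioid alone. In a model of dose counts (Poisson with gamma frailty, shape 4; step 3 if any strong-opioid dose is given, otherwise step 2), assumed means of 4 versus 6 doses give power of about 0.56 on dose and 0.05 on score. In that case nearly everyone is on step 3 by assumption. Means of 0.7 versus 2 doses give about 0.94 and 0.75.
- **That last observation carried forward would fill a drug-free day with the previous score.** That rule is for missing values. Drug and dose are recorded daily, so a day without analgesics is observed.
- **That stopping analgesia early earns no credit.** This depends on the coding. If drug-free days add nothing, stopping early lowers the sum.
- **That adding the codes distorts every comparison.** Treating step 3 as three times step 1 has no effect on a rank test of the daily score. It matters only for the cumulative sum.

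**Conclusion.** The point holds in a limited form. The article collects drug and dose but defines analgesic use by step alone, so differences in opioid dose within a step are invisible to the stated endpoint. The cumulative score is also ambiguous, because a drug-free day has no stated value (6 or 9 in the worked example).

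How much is lost depends on the unknown share on strong opioids. For a 2-fold dose ratio under the assumptions above, dose has power of 0.99, 0.70 and 0.17 at shares of 100%, 80% and 50%, against 0 to about 0.05 for the score. The gap is large if most patients are on strong opioids and small if about half are. Those figures rest on the assumed log-dose SD of 0.6 and on equal shares in both arms, and they concern a single day's score, not the multi-day sum.

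This is a secondary endpoint; the primary test and the sample size are unaffected. It still deserves a change, because analgesia is adjusted by ward judgment and the 24-hour dose is needed to interpret the primary VAS.

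**What to change.** Using the data already recorded:

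1. Define analgesic use as total opioid dose in morphine equivalents for 0-24 h and through POD 5, with non-opioid dose reported alongside.
2. Score a day without analgesics as 0 on the ladder scale.
3. Keep the daily and cumulative ladder scores as descriptive measures.
4. Report 24-hour opioid dose by arm next to the primary VAS result.

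A combined rank analysis of pain and opioid dose could be added as support, but the point does not depend on it. The cost is one conversion table, fixed before analysis, and one derived variable. Data collection, patient care, the primary test and the sample size do not change. If the full protocol or analysis plan already defines a dose summary, the endpoint text should be brought into line with it.
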